#### Primary endpoint

The associations between polymorphisms in adiposity-relevant genes (e.g. *FTO, MC4R, TMEM-18*) on the changes in BMI and BMI-SDS after a controlled lifestyle intervention (4 to 6 weeks) in overweight and obese children and adolescents.

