**Physical examination**							

Anthropometry*	+	+	+	+	+	+	+

Pubertal stage (Tanner)	+		+	+	+	+	+

Comorbidities/Medication	+	+	+	+	+	+	+

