### Statistical considerations

Associations between polymorphisms in adiposity-relevant genes (*FTO, MC4R, TMEM-18*) and changes in BMI(-SDS) from the start to the end of the intervention, will be assessed using analysis of covariance (ANCOVA) models comparing mean changes in BMI(-SDS) between the two groups of homozygous and the group of heterozygous children adjusted for age, sex and baseline weight. A two-sided level of significance of α = 0.05 will be used. For pairwise group comparisons, two-sample t-tests will be conducted using a Bonferroni-adjusted level of significance of α* = 0.0167.

Middle and long-term associations between genes and measures of interest such as weight change, physical fitness and physical activity will analogously be analysed in an explorative manner. Linear regression models including all relevant genes plus baseline weight, age and sex will be fit into estimate predictive models for the expected short and long-term weight changes. Predictive accuracy of the models and most relevant genes will be assessed using re-sampling methods (e.g. bootstrap) [42]. To estimate the influence of genes on relevant measures over time, a mixed model will be fit to account for multiple measures in the same participants. Missing values will be replaced using multiple imputation methods based on observed values with varying assumptions. Differences in the results obtained by different imputation strategies will be reported and discussed.

With a sample size of 1,500 children the study is sufficiently powered to detect significant differences in all pairwise comparisons between allele groups on an adjusted two-sided level of significance of α* = 0.0167, if the true difference in means is at least half of the common standard deviation translating to an effect size of 0.5 (power > 90% for each pairwise comparison). The sample size calculation is based on the assumption that the distribution of alleles leading to the smallest subgroups will be 70%, 25% and 5%, hence the smallest sample sizes for pairwise comparisons will be 375 versus 75 children. Sample size estimation was conducted for a two-sample t-test with unequal group sizes using the software nQuery (Version 7.0).

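### The pairwise genotype comparisons use unadjusted t-tests although the three-group test is an adjusted ANCOVA; the contrasts should come from the same model

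*Protocol article*

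**What the plan says.** All of this is in the protocol article, Statistical considerations.

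- **Three-group test.** An ANCOVA is used, "comparing mean changes in BMI(-SDS) between the two groups of homozygous and the group of heterozygous children adjusted for age, sex and baseline weight". On the level: "A two-sided level of significance of α = 0.05 will be used".
- **Pairwise tests.** "For pairwise group comparisons, two-sample t-tests will be conducted", with the level Bonferroni-corrected to 0.0167. No covariate is named for this step, and a two-sample t-test takes none.
- **Power.** With 1,500 children, each pairwise comparison is said to have more than 90% power for a difference of 0.5 SD at the adjusted level. The smallest comparison is 375 versus 75, from an assumed 70/25/5 split. The calculation was done for a two-sample t-test with unequal groups.

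The Primary endpoint section names change in both BMI and BMI-SDS over the 4 to 6 week intervention as the outcome.

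**The concern.** The plan decided that genotype groups should be compared "adjusted for age, sex and baseline weight", and then makes the comparisons of most interest without any of these covariates. Two things follow.

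1. **Precision.** Children are 6 to 19 years old and differ widely in starting size. Any part of the variation in change that age, sex and baseline weight explain stays in the error term of the t-test, although the data to remove it are in the planned model.
2. **Consistency.** The ANCOVA compares genotypes at equal age, sex and baseline weight. The t-test compares raw mean changes. The two targets coincide only if the covariates are unrelated to genotype. The Background (The role of genes) reports an *FTO* variant associated with higher BMI in children, so baseline weight may well be related to genotype. The global result and its follow-up contrasts would then describe different quantities.

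At stake is the sharpness and coherence of the primary genotype comparisons, above all those with the small minor-homozygote group.

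**Working it through.** **Inputs from Statistical considerations:** N = 1,500; split 70/25/5, so 1,050, 375 and 75 children; difference d = 0.5 SD; two-sided level 0.05/3 = 0.0167.

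**Step 1: reproduce the stated power.** The non-centrality is d × √(n1·n2/(n1+n2)).

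- 375 vs 75: 0.5 × √(375 × 75/450) = 0.5 × √62.5 = 3.95. Against a critical value of about 2.39 (normal), power is 94.1%; with the noncentral t distribution it is 93.9%.
- 1,050 vs 75: 0.5 × √(1,050 × 75/1,125) = 0.5 × √70 = 4.18. Noncentral t power is 96.3%.
- 1,050 vs 375: above 99.9%.

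All three exceed 90%, as stated.

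**Step 2: the same contrast from the ANCOVA.** If the covariates explain a share R² of the variance of change and are close to unrelated to genotype, the residual SD is SD × √(1 − R²), and the non-centrality is divided by √(1 − R²). The article gives no R², so the values below are assumptions. For 375 vs 75 at level 0.0167 (noncentral t):

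| R² (assumed) | Non-centrality at 0.5 SD | Power at 0.5 SD | Power at 0.3 SD | Difference detectable with 90% power |
|---|---|---|---|---|
| 0 (t-test) | 3.95 | 93.9% | 48.8% | 0.466 SD |
| 0.1 | 3.95/√0.9 = 4.17 | 96.1% | 53.9% | 0.442 SD |
| 0.2 | 3.95/√0.8 = 4.42 | 97.8% | 59.9% | 0.417 SD |
| 0.3 | 3.95/√0.7 = 4.73 | 99.0% | 66.7% | 0.390 SD |

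In sample-size terms the gain is 1/(1 − R²): a factor of 1.11 at R² = 0.1 and 1.43 at R² = 0.3.

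**Step 3: can the adjusted and unadjusted contrasts lead to different decisions?** A simulation took 375 vs 75 children, a true difference of 0.3 SD and 3,000 runs per setting. It assumed a correlation of 0.2 to 0.6 between baseline BMI and change, and of 0.7 to 0.95 between weight and BMI. Baseline was unrelated to genotype, and age and sex were not modelled.

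- Power of the t-test: about 46% to 50%.
- Power of the contrast adjusted for baseline weight: about 48% to 68%.
- Power of the contrast adjusted for baseline BMI: about 49% to 72%.
- The t-test and the weight-adjusted contrast fell on different sides of 0.0167 in about 4% to 25% of runs.

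Most of the gain comes from adjusting at all. Moving from baseline weight to baseline BMI adds less in most settings.

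**The case against.** The strongest reply is that nothing stated is wrong. The study is sized for a two-sample t-test and the pairs are analysed by a two-sample t-test, so calculation and analysis match, and the power claim is met. At the plan's own 0.5 SD the gain is from 93.9% to 96–99%, in a comparison already above target. The gain also rests on an assumed R² that could be near zero, particularly for BMI-SDS, which is already a standard deviation score. All of this stands, and it limits the weight of the point.

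It is also true that adjusted contrasts do not remove every disagreement. A significant global F-test with no significant Bonferroni contrast can occur within one ANCOVA. The 4% to 25% above compares two versions of the same contrast, at 0.3 SD and under assumed correlations; it does not compare the contrast with the global test. What adjusted contrasts do remove is the disagreement that comes from using two different models.

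Three stronger readings are tempting, and the article does not support them.

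- **That the t-tests are confounded by starting BMI.** Genotype is fixed before baseline BMI. On the article's own account variants influence BMI, which makes starting BMI a possible mediator and not a common cause. The unadjusted contrast answers a legitimate question about the total association.
- **That baseline weight is the wrong covariate.** Height varies, so 85 kg is a BMI of 85/1.55² = 35.4 at 155 cm and 85/1.75² = 27.8 at 175 cm. But weight together with age and sex is a partial proxy for BMI, and the simulated gain from replacing it is modest. Conditioning on baseline BMI instead also changes what is estimated. It is a choice, not a correction.
- **That pubertal stage ought to be a covariate because Table 4 shows it recorded at Visit 1.** Nothing in the article shows that it predicts change over 4 to 6 weeks beyond age.

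**Conclusion.** The point holds as one of efficiency and consistency. The plan adjusts the three-group test and drops the same adjustment from the pairwise comparisons, without giving a reason.

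The cost depends on how well age, sex and baseline weight predict change, which the article does not say. For an assumed R² of 0.1 to 0.3 the t-tests give up about 2 to 5 percentage points of power at 0.5 SD (93.9% against 96.1–99.0%) and about 5 to 18 points at 0.3 SD (48.8% against 53.9–66.7%). At R² near zero there is practically no loss. These figures also assume that the covariates are close to unrelated to genotype and that the adjusted difference is as large as the raw one.

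A reader might infer that the study is underpowered or that its genotype contrasts are invalid. Neither follows: the power above 90% is correct for the tests as planned, and the unadjusted difference is interpretable. The change is still worth making, because it uses the plan's own model and data already collected.

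**What to change.** In Statistical considerations, replace the two-sample t-tests by the three pairwise genotype contrasts estimated from the same ANCOVA (age, sex, baseline weight), at the same Bonferroni level of 0.0167. Keep the t-test calculation as the power statement, and call it conservative for the adjusted contrasts provided the covariates are close to unrelated to genotype.

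Optionally, add a sensitivity analysis that puts the baseline value of the analysed outcome in place of baseline weight: baseline BMI for change in BMI, baseline BMI-SDS for change in BMI-SDS. State that it estimates the genotype association at equal starting BMI or BMI-SDS.

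The cost is a few lines of text. Weight and height are measured at Visit 1, so no new data, visits or participants are needed. Recruitment began in January 2006 and a first step of genotyping is reported as done, so the change should be a dated and justified amendment that says whether genotype results on the outcome had already been seen.

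### Fixed Bonferroni at 0.0167 for the three pairwise genotype tests is valid and meets the stated power, but a three-group step-down rule would find more pairs within the same 5% familywise limit (optional gain).

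*Protocol article*

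**What the plan says.** The Statistical considerations section of the Protocol article plans an ANCOVA "comparing mean changes in BMI(-SDS) between the two groups of homozygous and the group of heterozygous children", adjusted for age, sex and baseline weight. For that analysis, "A two-sided level of significance of α = 0.05 will be used". For pairs of genotype groups, "two-sample t-tests will be conducted using a Bonferroni-adjusted level of significance of α* = 0.0167".

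The power statement rests on the pairwise level. With 1,500 children the study is described as "sufficiently powered to detect significant differences in all pairwise comparisons between allele groups on an adjusted two-sided level of significance", "if the true difference in means is at least half of the common standard deviation translating to an effect size of 0.5", with "power > 90% for each pairwise comparison". The least favourable genotype split is taken as 70%, 25% and 5%, so the smallest pair is 375 versus 75.

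The section does not make the pairwise tests conditional on the ANCOVA, and it gives no reason for the single-step form, such as simultaneous confidence intervals.

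**The concern.** A fixed level of 0.05/3 charges every pair for three comparisons, whatever the other pairs show. With three means this is stricter than a 5% familywise limit requires. If one pairwise equality is false, at most one of the other two can be true, because two true equalities would force the third. Once one pair has been declared different, at most one false positive is still possible, and the remaining pairs need no further division of alpha.

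At stake is how many of the three contrasts are identified, above all the contrast of heterozygotes with the rare homozygotes, where only 75 children are assumed on one side. The pairwise contrasts say which genotypes differ, and the plan's only power statement is made for them.

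**Working it through.** **Inputs (Statistical considerations).** N = 1,500; split 70/25/5%, so 1,050, 375 and 75 children; difference 0.5 SD; two-sided pairwise level 0.05/3 = 0.0167; two-sample t-test.

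**The plan's own figure.** Noncentrality = d × √(n1·n2/(n1+n2)). For 375 versus 75 this is 0.5 × √(28,125/450) = 0.5 × √62.5 = 3.953. With 448 degrees of freedom the critical value at 0.0167 is 2.402, and the noncentral t gives power 93.9%. The pair 1,050 versus 75 has noncentrality 4.183 and power 96.3%; 1,050 versus 375 has noncentrality 8.31 and power close to 100%. The claim of more than 90% for each pair is correct.

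**Why the step-down rule is valid.** The rule: order the three p-values, test the smallest at 0.05/3 and, if it is significant, test each of the other two at 0.05. By closed testing, a pair may be rejected when every hypothesis containing its equality is rejected at 5%. With three groups, any two equalities together amount to all three means being equal. So only two kinds of test are needed: the global null (smallest p-value at 0.05/3) and each single equality at 0.05. Any p-value below 0.0167 passes both, so every Bonferroni rejection is kept.

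**Power and error.** Simulation of 400,000 trials per pattern, groups 1,050/375/75, SD 1, pooled t-tests. Means are in SD units, in the order common homozygote, heterozygote, rare homozygote. The patterns are assumptions; the plan gives only the 0.5 SD pairwise difference.

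| Means | Quantity | Bonferroni | Step-down |
|---|---|---|---|
| 0, 0, 0.5 | power, 375 vs 75 | 93.9% | 96.5% |
| 0, 0, 0.5 | at least one rejection | 97.3% | 97.3% |
| 0, 0.5, 1.0 | power, 375 vs 75 | 93.9% | 97.6% |
| 0, 0.25, 0.5 | power, 375 vs 75 | 34% | 50% |
| 0, 0.25, 0.5 | all three pairs found | 31% | 49% |
| 0, 0.25, 0.5 | at least one rejection | 99.7% | 99.7% |
| 0, 0, 0 | familywise error | 4.0% | 4.0% |
| 0, 0, 0.5 | familywise error | 1.7% | 5.0% |

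Direct check: at level 0.05 the critical value is 1.965. Noncentrality 3.953 then gives 97.6%, and 0.25 × √62.5 = 1.976 gives 50.5%. These are the step-down powers for 375 versus 75 when another pair is almost certain to be rejected first.

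The pattern 0, 0.5, 1.0 is the narrowest spread in which all three pairs differ by at least 0.5 SD. If the two homozygous groups are only 0.5 SD apart with heterozygotes midway, the adjacent differences are 0.25 SD. That is half the design difference, and there the choice of rule matters most.

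**The case against.** The case for leaving the plan alone is substantial.

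- **Nothing is wrong as written.** The procedure is valid, the study was sized on the same level, and the target is met. A reader might infer that the study is underpowered or the power statement faulty; the plan's own figures show otherwise. This stands.
- **The large gains come from effects the plan does not use.** At the design difference the gain is about 3 to 4 points; the jump from 34% to 50% belongs to an assumed pattern with half that difference. This stands, and the larger figures are illustrations only.
- **The overall test is untouched.** The ANCOVA at 0.05 stays as it is, and the chance of at least one pairwise rejection is identical under both rules. The gain is only in further pairs once one has been found. This stands.
- **The gain is not free.** A reader might infer that Bonferroni throws power away for nothing. It does give tests and simultaneous intervals that agree, although the article does not claim that use. Under the step-down rule a pair can be declared different while its 98.3% interval includes zero. When one pair is truly equal and the others clearly differ, the false-positive rate rises from about 1.7% to 5%.
- **Several genes and two outcomes are tested.** The section names three genes and both BMI and BMI-SDS, and states no correction across them. Assume three independent genes, each with one truly equal pair and a near-certain first rejection. The chance of at least one false pair is then 1 − (1 − 0.0167)³ = 4.9% with Bonferroni and 1 − 0.95³ = 14.3% with the step-down rule. This is a fair reason to keep the stricter rule. However, Bonferroni over three pairs was not built to control error across genes, and neither rule does so.

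It may also be asked how the pairwise rule relates to the ANCOVA if the two disagree. The present text leaves that question open too. The step-down rule controls its own error without the ANCOVA as a gate, so it adds no new difficulty.

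**Conclusion.** The point holds as an optional efficiency gain, not as an error. Fixed Bonferroni at 0.0167 is valid and delivers the power claimed. For exactly three groups the step-down rule rejects all that Bonferroni rejects, sometimes more, and keeps the familywise error at 5% within one polymorphism and one outcome. For 375 versus 75 the gain is about 3 to 4 points at 0.5 SD. It reaches about 17 points for that pair, and 18 for finding all three, under the assumed 0, 0.25, 0.5 SD pattern.

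The figures rest on the plan's 70/25/5% split, a common standard deviation, all 1,500 children analysed, and unadjusted t-tests as planned.

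**What to change.** Leave the ANCOVA at two-sided 0.05. Replace the sentence on pairwise tests with: within each polymorphism and outcome, the three pairwise p-values are ordered; the smallest is tested at 0.05/3; if it is significant, each of the other two is tested at 0.05; otherwise no pair is declared different. If 98.3% intervals are shown, say that they are conservative and may not match the later-step decisions.

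The sample size and power statement stand, because every Bonferroni rejection is retained. No further children or data are needed.

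Timing matters. Recruitment began in January 2006 and first-step genotyping is reported as done (Recruitment process; Genetic analysis), and the article does not say whether genotype-outcome results have been examined. The change should be made and dated before they are. If they have been, keep Bonferroni as the decision rule and label any step-down result as supplementary. The other cost is the higher error for a truly equal pair, up to the nominal 5%; a team that wants the stricter rule for that reason can keep it and say so.

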## Discussion

This manuscript provides an outline of the rationale and the design of the LOGIC-trial, which is the first study that evaluates the short, middle and long-term effects of an inpatient weight-loss program in association with genetic factors in a large group of children and adolescents (aimed sample size n = 1,500) and includes follow-up measurements over 10 years. Hence, this study will allow the investigation of important determinants of successful weight-loss, particularly the role of a specific genetic predisposition. To achieve this, a large amount of data is being collected, on anthropometry, blood parameters (adipokines and inflammatory markers), physical fitness, physical activity and quality of life.

To our knowledge, only 24 evaluated inpatient programmes have been published, of which merely 14 carried out follow-up assessments. In all studies but one the follow-up periods lasted no longer than three years. No study has ever carried out follow-up measurements after more than five years following an inpatient weight-loss program [18,22-24]. Therefore, our study is unique particularly regarding the 5 and 10 year follow-up measurements and allows investigating the tracking of the effects of an inpatient lifestyle intervention from childhood to adolescence and adulthood. In addition, the large sample size of 1,500 children allows a thorough investigation of the genetic questions of interest. The question of genetic predisposition is particularly interesting regarding obesity and weight change, as obesity is considered as a polygenic syndrome with various SNPs involved. To date, however, the impact of the SNP's on the individual responses to obesity treatment in children is still unclear. The studies that have shown an influence of genetic factors on changes in body weight induced by a lifestyle intervention in children [25-30] had relatively small sample sizes (n = 236 to n = 519) and have shown inconsistent results. A clear advantage of the LOGIC-trial protocol is the inclusion of adipokines and inflammatory markers, as well as objective measures of physical fitness, which will allow investigations of the associations between changes in body weight, inflammation and physical fitness. These investigations are of particular relevance in light of potentially important links between these parameters as indicated by a recent review [7]. Some studies have shown relevant associations between adipokines and weight-loss induced by lifestyle interventions [43-46], whereas particularly the results concerning the associations between adipokines and physical fitness are equivocal. This can be explained by the small sample sizes and different outpatient study settings [47-51]. A further strength of the LOGIC-trial is that all anthropometrical parameters are taken by either a nurse or a general practitioner. This avoids the underestimation of body weight that is often observed in self-reports [52]. The inpatient setting is standardised in that participants are living in a controlled environment with similar dietary and exercise conditions and intervention. Such a controlled setting is particularly important for the investigation of the influence of genetic factors, which can be strongly confounded by environmental conditions [15].

Our study has a few limitations, which cannot be completely avoided in this real-life setting. This is an observational study and not a randomized controlled trial. In a randomized design with a 10 year follow-up time it would be ethically questionable to randomize children into an inpatient weight-loss programme and a control group, as the children from the control group would not be allowed to take part in the lifestyle intervention during that time. In addition, the primary intention of this study is to investigate the inter-individual variability of the effects of the intervention depending on the children's genotypes, which does not necessarily require a control group. For cross-sectional analyses, we use an age-matched sample of normal weight children of a school-based intervention study [53] as well a cohort of young athletes, who are recruited at the *Department of Prevention, Rehabilitation and Sports Medicine, Technical University of Munich*.

As we recruit a selected cohort of children who take part in a specialized obesity program it has to be considered that data from clinical samples may not be representative for general populations. Furthermore, although we do have objective physical activity measurements during the intervention, long-term physical activity is assessed by questionnaires. It has been planned this way as we require a standardised physical activity assessment method that can be carried out by all participants for every follow-up measurement during this 10 year time period. Considering the inclusion of 1,500 children and in total seven measurement time points, objective physical activity measurements would have been almost impossible. Similar to the physical activity, nutritional behavior and intake is assessed by questionnaire. Again, more objective measurements such as dietary records would have been optimal but logistically difficult to integrate. In order to maintain high the compliance of the participants we tried to develop and carry out follow-up examinations that are valid, practical and not too time consuming. Therefore we are not using a detailed food frequency questionnaire.

In summary, this is the first lifestyle intervention study with a detailed assessment of short, middle and long-term weight changes, physical fitness, cardiometabolic risk factors including both inflammatory markers and adipokines in a large cohort of overweight and obese children. Apart from elucidating the short-term effects of this supervised weight-loss program, this study will provide the outstanding opportunity to investigate the tracking of the immediate effects of a lifestyle intervention on body weight and the cardiometabolic risk profile from childhood into adolescence and adulthood under consideration of the influence of genetic predisposition. This will contribute to a better understanding of inter-individual differences in the regulation of body weight and thus may lead to an optimization of personalized treatment strategies for childhood obesity.

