### The role of genes

Weight gain due to an increase in adipose tissue is the result of an imbalance between energy expenditure and energy intake. This balance can be influenced by both physical activity and caloric intake, which can be dependent on social, psychological and other behavioral factors. In addition, genes have been shown to play a fundamental role in the regulation of body weight [1,11]. Apart from very rare monogenetic disorders [12], a genetically determined higher risk for obesity can often be attributed to a polygenetic pattern involving different single nucleotide polymorphisms (SNP's). For instance, variations in the *FTO*-gene seem to have an effect on the development of early onset obesity. Likewise, a study by Frayling et al. has shown that a single-nucleotide polymorphism of the SNP *rs9939609*A allele is associated with an increased risk of overweight (odds ratio 1.18; 95% CI = 1.13 to 1.24) and obesity (odds ratio 1.31; 95% CI = 1.23 to 1.39), increasing the risk by 20-30%. Additionally, the A allele of the *rs9939609 SNP *has been found to be associated with an increased body mass index (BMI) in 7 year old children and to also determine obesity during puberty and beyond [13]. Furthermore loci associated with neuronal pathways (*TMEM18, GNPDA2, SH2B1, NEGR1*) have recently been identified to be associated with childhood obesity [14]. It has to be noted though that these genetic predispositions may only lead to an obesity phenotype in the presence of an obesogenic environment, and therefore this association may be modified by a lifestyle intervention [15,16].

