#### Secondary endpoints

The short (4 to 6 weeks), middle (6 to 12 months) and long-term (2, 5 and 10 years) effects of the intervention on the below-listed parameters and their associations with polymorphisms in adiposity-relevant genes (*e.g. FTO, MC4R, TMEM-18*):

• anthropometric parameters

• parameters of lipid and glucose metabolism

• adipokines and inflammatory markers

• physical fitness

• physical activity

• dietary behavior and intake

• health-related quality of life

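### Endpoints from 6 months to 10 years are called effects of the intervention, by genotype, but no untreated obese children are followed, so they can only show change in a treated cohort

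*Protocol article*

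**What the plan says.** All references are to the protocol article.

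- **Primary endpoint.** Genotype is related to change in BMI and BMI-SDS over the 4 to 6 week programme, and the endpoint is worded as an association.
- **Secondary endpoints.** These are "The short (4 to 6 weeks), middle (6 to 12 months) and long-term (2, 5 and 10 years) effects of the intervention" on a list of parameters that starts with anthropometry, and "their associations with polymorphisms in adiposity-relevant genes".
- **Statistical considerations.** The text plans "Middle and long-term associations between genes and measures of interest such as weight change", to be analysed in the same way as the primary endpoint but as exploratory work. The primary ANCOVA adjusts for sex, age and weight at baseline. A mixed model for repeated measures is also planned.
- **Discussion, limitations.** The study is acknowledged to be observational and non-randomised. An ethical reason against a randomised control group over 10 years comes first. The text then adds that the primary intention is "to investigate the inter-individual variability of the effects of the intervention depending on the children's genotypes", "which does not necessarily require a control group". The comparison samples are normal-weight schoolchildren and young athletes, for cross-sectional use.
- **Discussion, strengths and summary.** The study is said to allow "tracking of the immediate effects of a lifestyle intervention on body weight" and the cardiometabolic risk profile into adulthood, and its results may help to optimise personalised treatment.
- **The role of genes.** The *FTO* A allele is reported to be associated with higher BMI at age 7 and "to also determine obesity during puberty and beyond". The same section says that lifestyle intervention may modify the genetic association.

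**The concern.** An effect of the intervention is a contrast between the course with the programme and the course without it. A genotype-dependent effect is the difference between genotypes in that contrast. The cohort supplies only the treated course. Over a few weeks under inpatient control the untreated course can be taken as nearly flat, so little is lost. Over 6 months to 10 years it cannot.

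Two conclusions are at stake. The mean change at 2, 5 or 10 years could be reported as a lasting programme effect. A genotype difference at those visits could be reported as better or worse response to treatment and carried into the personalised-treatment aim, although the same difference could arise from genotype-related weight development that has nothing to do with the programme.

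**Working it through.** **1. What is wanted and what is observed.** For genotype g and time t, let T_g(t) be the mean change from Visit 1 with the programme and U_g(t) the mean change the same children would have had without it.

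- Programme effect: T_g(t) − U_g(t). Observed: T_g(t).
- Genotype-dependent effect, genotypes a and b: [T_a − U_a] − [T_b − U_b]. Observed: T_a − T_b.
- Observed minus wanted: U_a(t) − U_b(t), the genotype difference in untreated change.

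No participant contributes to U. The two comparison samples are not obese and are used cross-sectionally, so they do not supply it either.

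**2. Is U negligible after discharge?** The document gives reasons to doubt it.

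- *Puberty:* entry age is 6 to 19 years, so age at Visit 7 is 6 + 10 = 16 to 19 + 10 = 29 years. Many younger entrants pass through puberty during follow-up, the period to which the Background ties the *FTO* allele.
- *Regression to the mean:* entry requires high BMI and repeated failure of outpatient therapy (Table 1).
- *Later treatment:* parents are asked to arrange outpatient psychological treatment after discharge (Table 3).

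**3. Does the adjustment remove it?** No. BMI-SDS removes average growth for age and sex. Covariates for sex, age and weight at baseline align the genotype groups at entry. Neither removes a later difference in course that is specific to genotype.

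**4. Why the inpatient window differs.** If drift accrued evenly over 10 × 52 = 520 weeks (an assumption), 6 weeks would carry 6/520 = 1.2% of it.

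**5. The plan's own power figure.** Group sizes are 1,500 × (0.70, 0.25, 0.05) = 1050, 375 and 75, and α* = 0.05/3 = 0.0167. For standardised difference d the noncentrality is d / √(1/n₁ + 1/n₂). For 375 v 75 at d = 0.5 this is 0.5 / √0.016 = 3.95. Against a critical value of 2.394, power is 94.1% (normal) or 93.9% (noncentral t). The other pairs give 96.3% (1050 v 75) and above 99.9% (1050 v 375). The stated figure of more than 90% is reproduced and is not in dispute.

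**6. Illustration of misattribution.** Suppose the programme effect is identical in every genotype and untreated change differs by d SD between the two groups compared. The values of d are assumptions, because the documents give none. The probability of a significant pairwise difference at 0.0167, from the same formula with noncentral t and full retention, is:

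| d (SD) | 375 v 75 | 1050 v 75 | 1050 v 375 |
|---|---|---|---|
| 0 | 1.7% | 1.7% | 1.7% |
| 0.1 | 5.5% | 6.0% | 23% |
| 0.2 | 21% | 24% | 82% |
| 0.3 | 49% | 55% | 99.5% |

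With 50% retention and d = 0.2 the figures are 10%, 11% and 48%. A larger sample makes such a finding more likely, not less. The table shows how the design would behave under drift. It does not show that drift exists.

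**The case against.** The other side has real points.

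- **The control-group sentence is qualified.** It says *not necessarily*, it concerns the primary intention, and it follows a separate ethical argument. The only primary endpoint is the 4 to 6 week one, where the argument roughly holds. This stands. A reader might infer that the protocol declares a control group unnecessary at every horizon, or that the primary analysis is undermined; the text supports neither. But the sentence speaks of effects of the intervention without a time limit and directly follows a passage about 10-year follow-up, so its scope should be stated.
- **The Background does not say that carriers diverge without treatment.** It reports associations with BMI and obesity, not different rates of change among children already obese, and it allows that intervention may modify the association. This stands too. Divergence is plausible from the text but not asserted there. Modification by lifestyle is the hypothesis, and testing it over years needs the unmodified course as a reference.
- **The limitation is disclosed and the long-term gene analyses are exploratory.** Disclosure of a non-randomised design and exploratory status are both to the plan's credit. Neither withdraws the effect wording: exploratory status bears on strength of evidence, not on attribution. The predictive models do not need an untreated arm and are not affected.
- **No passage commits the authors to reading a genotype difference as poor response.** That is correct. The point is that the endpoint wording invites this reading.

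**Conclusion.** The point holds for the secondary endpoints after discharge. In a cohort where everyone is treated, the middle and long-term results are changes and genotype associations; they cannot be attributed to the programme or read as genotype-dependent response. This rests on the untreated course not being negligible, and not known to be equal across genotypes, over 6 months to 10 years. The document makes that plausible but does not quantify it.

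The size is therefore unknown. A reader might want to express assumed drift as a share of the −0.17 BMI-SDS follow-up change quoted in the Background for inpatient programmes. That would set a between-genotype difference over up to 10 years against a mean within-cohort change at 1 to 2 years, so it measures nothing useful.

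The primary endpoint, its ANCOVA and the power statement are not affected. The change is one of wording, but it alters what the trial may conclude at 2, 5 and 10 years.

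**What to change.** 1. **Secondary endpoints:** keep *effects of the intervention* and genotype-dependent response for Visit 1 to Visit 2 only. Name the later endpoints *changes after the intervention and their association with genotype in a treated cohort*.
2. **Discussion, limitations:** state that the control-group argument applies to the inpatient window only.
3. **Discussion, strengths and summary:** bring the tracking and personalised-treatment statements into line, so that long-term data are described as weight course after treatment.
4. **Optional:** report change from Visit 1 to Visit 2 separately from change from Visit 2 to Visit 7. This distinguishes response during the programme from later course, but it supplies no untreated reference and does not by itself solve attribution.

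No new patients, visits or measurements are needed, and no randomised control group is being asked for. The cost is a weaker long-term claim.
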